### Measurement

#### Overview

The primary outcomes of the study will be the social and emotional well-being of older adults, and the secondary outcomes will be the benefits to the young adult volunteers. Social well-being will be measured by quality of life and loneliness, whereas emotional well-being will be measured by affects (positive and negative) and resilience. Regarding social well-being, quality of life is a relatively global and stable phenomenon that comprehensively measures people’s psychosocial well-being [46]. Recent studies suggest that loneliness, which represents the negative subjective experience of the inadequacy of social relationships, is a factor in evolutionary fitness across the life span [47] and is a good indicator of social well-being [48]. Regarding emotional well-being, PA and NA have been used as general dimensions to describe affective, emotional components of subjective well-being [49]. Resilience, as an important indicator of emotional well-being, assesses one’s ability to bounce back from or adapt to stressful situations or crises, such as having been diagnosed with ADRD [10,11]. Young adult volunteers will be asked about their attitude toward aging and knowledge and awareness about the ADRD disease. Demographic information about each dyad, such as age, sex, education, self-reported health, and so on, will also be collected in the pretest survey. A pilot test will be conducted on 3 volunteer dyads using assessment tools to evaluate participants’ possible overload impacts. In accordance with the input provided by pilot participants, the research team will review and make necessary modifications to the measurement selections within the initial 6 months of the project (preparation stage).

#### Primary Outcome Measurements for Older Adults

Quality of life of older adults in this study will be measured using Quality of Life–Alzheimer’s Disease (QoL-AD) [50]. The QoL-AD questionnaire consists of 13 items that cover various aspects including physical health, energy levels, mood, living situation, memory, family relationships, marital status, friendships, self-perception, ability to perform daily chores, engagement in enjoyable activities, financial situation, and overall life satisfaction. The higher the QoL-AD score, the better is the quality of life. Self-rating QoL-AD will be used, which had showed high reliability and validity [51,52].

Loneliness among older participants will be measured using the De Jong Gierveld Loneliness Scale [53]. This 6-item scale measures both emotional and social loneliness. This instrument has undergone validation in numerous countries, with validation studies encompassing various sexes and age groups and specifically including older adults. High scores indicate great loneliness. Reliability coefficients for both subscales were 0.81 to 0.85 [54].

The measurement of PA and NA in older adults will be conducted using the widely used Positive and Negative Affect Schedule (PANAS) [55]. PANAS assesses the respondent’s emotional state by inquiring about 10 positive and 10 negative emotions using a 5-point scale ranging from “Very slightly or not at all” to “Extremely.” This scale has demonstrated strong psychometric properties, with Cronbach α of .88 for PA and .87 for NA. Furthermore, PANAS has been validated across various cultures and languages worldwide, consistently exhibiting robust psychometric properties in multiple studies [49,56]. Total scores will be calculated for PA and NA, with high scores indicating more PA and NA, respectively.

The resilience of older adults will be measured using the Brief Resilience Scale [57]. The Brief Resilience Scale is recognized as one of the top and extensively endorsed resilience scales and recommended by Windle et al [58]. Extensive literature supports its high reliability and validity, as demonstrated by studies conducted by Smith et al [57,59]. A total of 6 items will be asked, and responses for each item ranges from 1 (*low resilience*) to 5 (*high resilience*). After reverse coding 3 items, total scores will be calculated for final analysis, with high score indicating more resilience.

#### Secondary Outcome Measurements for Young Adults

To measure the loneliness among young adult participants, we will use the De Jong Gierveld Loneliness Scale [53], following the same methodology used for measuring loneliness among older adults, as mentioned previously.

The Alzheimer’s Disease Knowledge Scale (ADKS) [60] will be used for the young adult volunteers. The ADKS is a comprehensive instrument consisting of a 30-item true or false scale. It can be completed in approximately 5 to 10 minutes and covers a wide range of domains, including risk factors, assessment and diagnosis, symptoms, disease progression, impact on daily life, caregiving, and treatment and management. Initial findings indicate that the ADKS exhibits satisfactory reliability, including test-retest and internal consistency and validity, including content, predictive, concurrent, and convergent validity. These results have been reported in studies conducted by Carpenter et al [60] and Spector et al [61]. Total scores will be calculated for final analysis, with high score indicating more knowledge.

To assess the young adult volunteers’ attitudes toward aging, the Fraboni Scale of Agism (FSA) will be used. The FSA, initially developed by Fraboni et al [62] and subsequently revised by Rupp et al [63], consists of 29 statements. Participants will rate their agreement on a 4-point Likert scale, ranging from 1 (*strongly disagree*) to 4 (*strongly agree*). The FSA has been widely used among college students and has demonstrated strong internal consistency and robust validity in previous studies [64,65]. Total scores will be calculated for final analysis, with high scores indicating more agism.

In addition, a 20-item questionnaire [25] will be developed to collect feedback from the young adult volunteers, covering (1) intervention preparation and organization, (2) intervention format and workload, and (3) perceived gains. Each item is rated on a 5-point scale (1=*strongly disagree* to 5=*strongly agree*), and the higher the score, the more positive the perception about the intervention.

#### Other Outcomes

Follow-up qualitative interviews will be conducted to explore participants’ overall experience with and perceptions about the intervention. On the basis of the results from the survey, we will select older and young adult participants who have the highest and lowest levels of changes in the outcomes for further qualitative interviews (10 dyads in total). Each generation’s experiences, perspectives, challenges, and suggestions regarding this intervention will be asked during these in-depth interviews.

### Data Collection Plan

Data will be collected at baseline, midpoint, end of the intervention, and 3 months after the intervention by telephone. A total of 3 GRAs will be trained to collect the data. Training on the assessment battery and interview techniques will be provided by PIs to GRAs. For the quantitative survey, after training, interrater reliability checks will be performed by 1 PI on pilot interviews of team members and participants (3 older adults and 3 college students not included in the final sample size), based on audiotaped interviews. For the qualitative interviews, training related to conducting interviews will be provided to GRAs, such as talking less and listening more, how to build rapport with the respondents, and how to handle unexpected emotions of participants. The GRAs will also pilot-test their qualitative interviewing skills based on role-plays with the research team. GRAs will have weekly supervision meeting with the PIs regarding participant recruitment and follow-up and survey assessments.

Several strategies will be used to track clients during the study and to minimize attrition. At the baseline and at each subsequent interview, participants will be asked to provide the names of 2 people who may know where they are if the researcher has difficulty in contacting them. We will also have the older participants’ MOW case managers as a backup point of contact. We will adopt the strategies of minimizing attrition in longitudinal studies [66], which results in 90% follow-up. These strategies (ie, getting several contacts, getting emails, reminder letters, and thank you letters) have proved to be useful in previous community-based studies conducted by the research team.

For individual missing responses on multiitem scales, we will compute scale scores by summing the available item scores as long as at least 80% of the item responses are available [67]. Missing data at the variable level will be handled through maximum likelihood imputation [67]. A concern with longitudinal research is that data are not missing randomly owing to systematic dropout. We will conduct attrition analyses to identify any factors systematically related to dropout and, if found, control for these effects in subsequent analyses. Any missing data that are random in nature, such as those that occur owing to random mistakes in data collection or entry and are not related to research staff or patient noncompliance, will be submitted to maximum likelihood estimation procedures to estimate those missing values. Maximum likelihood estimation for random missing data is a common and accepted procedure for missing data estimation [68,69]. If specific patterns of missing data are identified, we will further address missing values with multiple imputation. Multiple imputation will maximize accurate statistical inferences and allow for valid statistical inferences by appropriately accounting for the uncertainty caused by missing data [68,69].

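### Scale scores are an unprorated sum of the answered items, so a score with a permitted skipped item is too low by whatever that item would have scored

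*Protocol article*

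**What the plan says.** The item-level rule stands in the Data Collection Plan section of the protocol article: "we will compute scale scores by summing the available item scores as long as at least 80% of the item responses are available". No mean, proration or item-level imputation is attached to it. The next sentence moves to whole scores: "Missing data at the variable level will be handled through maximum likelihood imputation". The same paragraph then sends randomly missing data to maximum likelihood estimation and adds multiple imputation if particular patterns of missingness appear.

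The measurement sections confirm that several outcomes are analysed as totals. For PANAS, "Total scores will be calculated for PA and NA". For the Brief Resilience Scale, "After reverse coding 3 items, total scores will be calculated for final analysis". For the ADKS, "Total scores will be calculated for final analysis, with high score indicating more knowledge". The FSA is also totalled. For the QoL-AD and the loneliness scale the article gives only the direction of scoring, but both are multi-item scales and fall under the general rule.

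**The concern.** A sum over fewer items, not rescaled, equals a full sum with zero entered for each blank. Where items start at 1, zero is not an available answer, so the score falls for a reason unrelated to the participant's state. The direction depends on the scale. The score looks worse on the QoL-AD, positive affect and resilience, and better on negative affect and the FSA, where high values are unfavourable.

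All the primary outcomes for older adults are multi-item scales, collected by telephone on four occasions from people with cognitive impairment. Goals 1 and 2 compare the intervention group with its own pretest scores as well as with controls. A skip at one visit but not another therefore enters directly as apparent change. It also enters the selection for qualitative interview, which the Procedure section bases on the top and bottom tenth of changes.

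**Working it through.** The plan gives no figure for the effect of this rule, so there is nothing to reproduce. The check applies the rule to the article's own item counts.

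**Inputs.** QoL-AD: "The QoL-AD questionnaire consists of 13 items". Item coding is not given; 1-4 is assumed. Loneliness: "This 6-item scale measures both emotional and social loneliness". Item coding is not given. PANAS: "inquiring about 10 positive and 10 negative emotions using a 5-point scale". Coding 1-5 is assumed. Brief Resilience Scale (BRS): 6 items scored 1 to 5. FSA: 29 items scored 1 to 4. ADKS: 30 true/false items, taken as 1 if correct and 0 otherwise.

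**Formulas.** For k items, the number that must be answered is 0.8k rounded up, and the skips allowed are s = k minus that number. Loss = sum of the values the skipped items would have had. It lies between s × item minimum and s × item maximum, and at mid-scale is s × item midpoint. Scale range = k × (item maximum − item minimum).

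| Scale | 0.8k | Needed | s | Loss, min to max | Loss at mid-scale | Scale range | Share |
|---|---|---|---|---|---|---|---|
| QoL-AD (1-4 assumed) | 10.4 | 11 | 2 | 2 to 8 | 2 × 2.5 = 5 | 13 × 3 = 39 | 12.8% |
| PANAS, each subscale (1-5 assumed) | 8 | 8 | 2 | 2 to 10 | 2 × 3 = 6 | 10 × 4 = 40 | 15.0% |
| BRS | 4.8 | 5 | 1 | 1 to 5 | 1 × 3 = 3 | 6 × 4 = 24 | 12.5% |
| FSA | 23.2 | 24 | 5 | 5 to 20 | 5 × 2.5 = 12.5 | 29 × 3 = 87 | 14.4% |
| ADKS | 24 | 24 | 6 | 0 to 6 | depends on answers | 30 | at most 20% |
| Loneliness | 4.8 | 5 | 1 | coding not given | – | – | – |

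**Impossible values.** A complete BRS total cannot be below 6 × 1 = 6, yet five answers of 1 give 5. A complete FSA total cannot be below 29, yet 24 answers of 1 give 24. The out-of-range checks in the Statistical Analysis section could catch only such extremes; most short sums stay within range.

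**Raw against prorated sum.** This is an illustrative simulation with 200,000 draws per scale. It assumes a latent item mean of 3 (2 for the FSA), a latent item SD of about 1.1, an inter-item correlation of about 0.4 before rounding, the most skips allowed, and skips completely at random.

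| Scale | SD of full score | Raw-sum bias | In SDs | Prorated bias |
|---|---|---|---|---|
| BRS | 4.50 | −3.00 | −0.67 | +0.003 |
| PANAS subscale | 7.16 | −6.01 | −0.84 | −0.002 |
| FSA | 17.03 | −10.43 | −0.61 | +0.004 |

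The FSA figure is below 12.5 because the simulated item mean is 60.51/29 = 2.09, not 2.5.

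**From one score to the trial contrast.** If a share p1 of intervention scores and p0 of control scores at a visit lose L points each, the arm difference shifts by −L × (p1 − p0). It is zero when p1 = p0. The planned f = 0.22 is about d = 2 × 0.22 = 0.44 for two groups. To produce a spurious difference of that size, p1 − p0 would have to be about 0.44/0.67 = 0.66 (BRS), 0.44/0.84 = 0.52 (PANAS) or 0.44/0.61 = 0.72 (FSA), even with every affected score at the skip limit.

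The same formula holds for change over time within an arm, with the two visits in place of the two arms.

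**The case against.** The strongest defence is that the sentence is shorthand. It cites a source that is not available here, the article condenses a fuller plan, and scoring syntax is commonly left to that plan. Proration may have been intended. That cannot be excluded, but the article does not leave the matter open: it states an operative rule, and an analyst who follows it computes the wrong score.

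A second defence is that the maximum likelihood and multiple imputation steps cover these gaps. The first is introduced at variable level, and a short sum is then a computed, non-missing value. The later sentences are not expressly confined to whole scores. On the broader reading, the paragraph gives two rules for the same gap without saying which applies. Either way the text does not clearly repair the score.

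Three further objections stand and limit the point.

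- A reader might infer that every participant with a skipped item is scored too low on every outcome. The text does not support that. Only the scale and visit with the skip are affected; below 80% answered, the rule yields no score; and an item that would have scored zero loses nothing. A blank ADKS item costs a point only if it would have been correct. The effect on loneliness depends on coding that is not given.
- A reader might infer that the treatment effect is biased. That requires skipping to differ by arm. Arms are randomised and contact is matched, trained assistants administer the surveys by telephone, completeness is checked, and no rate of skipped items is reported.
- The QoL-AD marital item is a tempting example, since many clients live alone. Someone who skips it at every visit carries a roughly constant offset, which largely cancels from change.

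**Conclusion.** The rule is wrong as written. Any rating-scale score with a permitted skip is understated by the value of the missing item or items. At the skip limit and mid-scale answers this is 12.5% to 15% of the scale range, subject to the assumed coding for PANAS and QoL-AD. In the illustrative simulation it is 0.61 to 0.84 SD of the affected score.

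Those sizes belong to individual scores, not group means. What follows for the trial is added noise, distorted within-person change, and possible misplacement among the extreme changers chosen for interview. A spurious arm difference arises only if skipping differs by arm, and one as large as the planned effect would need an implausibly large difference in skipping. The frequency of skipping is unknown, so no bias in a primary contrast is shown. The rule should be corrected, but the documents do not show that the trial's conclusions depend on it.

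**What to change.** For the rating scales (QoL-AD, each PANAS subscale, Brief Resilience Scale, FSA and, once its item coding is stated, loneliness), replace the sum with (mean of answered items) × (number of items). Apply it per scale or subscale, after reverse coding, when at least 80% of items are answered. Otherwise set the score to missing and pass it to the variable-level missing-data method.

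Treat the ADKS separately: state whether a blank counts as incorrect or as missing. A blank may mean that the student did not know, in which case proration would inflate knowledge. Also say that the maximum likelihood and imputation steps apply to scores left missing after this rule, and report the number of skipped items by scale, visit and arm.

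The cost is about one line of scoring syntax per scale and no new data, since the Results section says cleaning is still under way. Interviews have already been held with selected dyads (8 of 27 in the intervention group), so rescoring can show whether that selection would have differed but cannot redo it. One manuscript is already published; whether it used these scores should be checked. The small downside is that proration assumes skipped items resemble answered ones.

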### Sampling and Recruitment Plan

Power analyses performed using G*Power 3.1.9 indicated that a total of 92 dyads (or 184 participants) are required to address our study objectives using a linear mixed model. This sample size estimate was based on a small effect size *(f*=0.22), a significance level of α=.05, β of .20, anticipated *r* over time of 0.30, and 5% attrition rate based on the findings of Chung [25], for 2-tailed tests.

Participants in this study will be community-dwelling older adults and undergraduate and graduate students (ie, young adult volunteers) enrolled at UTA. The eligibility criteria of the older adult participants include individuals who (1) are aged ≥65 years; (2) have cognitive impairment measured by the Ascertain Dementia 8 (AD8) [41]; (3) have decisional capacity as measured by the University of California, San Diego Brief Assessment of Capacity to Consent (UBACC) [42]; (4) are not participating in any other research protocol currently; and (5) can speak and understand English. The exclusion criteria for older adults are (1) participating in another trial, (2) having health issues that prevent them from participating in the study for 3 months, and (3) inability to commit to being available for the full 10 weeks of the intervention.

The older adult participants will be recruited through Tarrant County Meals On Wheels (MOW), which is a partner agency of the Area Agency on Aging of Tarrant County. Eligibility criteria to enroll in Tarrant County MOW is that a person must be homebound and have no one to help them on a regular basis. The Area Agency on Aging is very committed to expanding services and supports to people with ADRD, as many MOW clients with ADRD are living alone in Tarrant County. Moreover, studies suggest the need for additional research in the area of loneliness among clients using MOW [43]. Participant recruitment will begin with case managers and other MOW staff using their client database system to search for clients with ADRD who meet the study criteria. Next, case managers will contact potential study participants and then ask for permission to share their telephone number with a member of the UTA research team. The principal investigators (PIs) and graduate research assistants (GRAs) will follow-up with all the potential participants provided by MOW.

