For quantitative data analyses, descriptive analyses will first be conducted to provide the overall means and frequencies of key outcome variables for both older and young participants in the intervention and control groups. Fisher exact tests, Pearson chi-square tests, and independent samples *t* tests (2-tailed) will be computed to test for group differences that may be attributable to participants, such as age, sex, education level, income, and health conditions. If the groups significantly differ on any of these variables, the variable will be incorporated into the following analyses as a covariate, thereby controlling for potential influences that the covariate may have on the dependent variables. Moreover, in the event that at the culmination of this study, our sample sizes are unequal in the treatment groups or our outcome data are nonnormal, we will follow through with appropriate statistical corrections where necessary. Covariate-adjusted linear mixed models for repeated measures will be performed to compare the intervention and control groups over time for the major outcomes of older adults and young adult volunteers. The covariate will be any significant variable yielded from the univariate analyses, and the dependent variable will be the scores before the intervention, in the middle of the intervention, at the end of the intervention, and at 3-month follow-up. In this study, 95% CIs will be computed for each adjusted mean difference. The study α will be set to .05, with no adjustments for multiple comparisons owing to the preliminary nature of this study and the increased risk of type-2 error as a result of α adjustment [70].

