## Results

The study was funded in January 2021. Data collection started in May 2021 and ended in mid-2022. In total, 103 dyads were matched at the beginning of the intervention. Of the 103 dyads, 90 (87.4%) dyads completed the midtest survey and 64 (62.1%) dyads completed the posttest survey. Although a total of 92 dyads were planned to test the effectiveness of the intervention in this proposed study, the post hoc power analyses performed using G*Power 3.1.9 indicated that 64 dyads will yield sufficient power to test the interaction between groups over time (power=0.95), the changes over time (power=0.95), and the differences between the groups (power=0.71). These parameters are based on a small anticipated effect size (*f*=0.22), α=0.05, two-tailed, with measures correlated at r=0.30.

We also collected qualitative interview data for this study with selected dyads in the intervention group (8/27, 30%). Weekly reflection page from UTA student participants, weekly fidelity check forms, final digital story books, and final scrapbooks were also saved for future data analyses. We are currently engaged in data cleaning and analysis for both quantitative and qualitative data. One manuscript has already been published [73], and we anticipate publishing several more manuscripts reporting the results within the next 1-2 years.

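### Whether a baseline predictor of dropout enters the mixed model depends on an attrition screen with limited power; a short fixed covariate list would remove that dependence (minor)

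*Protocol article*

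**What the plan says.** The Data Collection Plan recognises the problem: "A concern with longitudinal research is that data are not missing randomly owing to systematic dropout". It then gives two conditional remedies.

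- Covariate adjustment: "We will conduct attrition analyses to identify any factors systematically related to dropout and, if found, control for these effects in subsequent analyses".
- Imputation: "If specific patterns of missing data are identified, we will further address missing values with multiple imputation".

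The unconditional default is likelihood-based: "Missing data at the variable level will be handled through maximum likelihood imputation". No test, threshold or list of factors is given for the attrition screen.

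The Statistical Analysis section describes a comparable selection step for baseline differences between arms: "independent samples *t* tests (2-tailed) will be computed to test for group differences", with variables that prove significant becoming model covariates. It also sets the level: "The study α will be set to .05, with no adjustments for multiple comparisons". The same section makes the scores at all four time points, including the one before the intervention, the dependent variable of the mixed model.

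The Results section reports the loss: "Of the 103 dyads, 90 (87.4%) dyads completed the midtest survey and 64 (62.1%) dyads completed the posttest survey". The Sampling and Recruitment Plan had assumed 5%.

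**The concern.** Adjustment for a cause of dropout is most useful when that cause also predicts the outcome, and this does not depend on whether a test in the same sample reaches significance. Under the stated rule, a variable that truly drives dropout but is not detected stays out of the model, and multiple imputation is not triggered either. Both added safeguards rest on detection.

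A mixed model fitted by maximum likelihood is valid when dropout depends only on what is in the model. If an omitted baseline factor predicts dropout, and predicts later outcome beyond the earlier scores, the comparison at the end of the intervention can be shifted. The risk is greatest when the factor acts differently in the two arms, because a shift common to both arms largely cancels. With 39 of 103 dyads lacking a posttest, the question is a practical one.

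**Working it through.** **Inputs from the protocol article.** Planned 92 dyads with 5% attrition, r = 0.30 and f = 0.22 (Sampling and Recruitment Plan). Reported 103 dyads matched, 90 at midtest and 64 at posttest (Results), so 13 and 39 were lost. Four measurements (Data Collection Plan).

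**Assumptions not in the document.** The screen is a two-sided t test at 5%. The completer-dropout difference is 0.5 SD, with 0.3 to 0.8 SD shown as a range. The factor correlates 0.4 with the outcome.

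**The plan's own figure first.** For 64 dyads, two groups and m = 4, between-group λ = f²·N·m/(1 + (m−1)r) = 0.0484 × 64 × 4/1.9 = 6.52, which gives power 0.71. For time and for the interaction, λ = f²·N·m/(1−r) = 0.0484 × 64 × 4/0.7 = 17.7, which gives 0.95. These match the stated 0.71, 0.95 and 0.95. They concern the treatment comparison, not the attrition screen, for which no power is stated.

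**Miss rate of the screen.** The noncentrality is δ = d·√(n₁n₂/(n₁+n₂)), and the miss rate is 1 minus the noncentral t power on n₁+n₂−2 degrees of freedom. At 64 v 39 and d = 0.5, δ = 0.5 × √(2496/103) = 2.46, so power is 0.684 and the miss rate 31.6%.

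| Completers v dropouts | 0.3 SD | 0.5 SD | 0.8 SD |
|---|---|---|---|
| 64 v 39 (posttest, reported) | 69% | 32% | 3% |
| 90 v 13 (midtest, reported) | 83% | 61% | 24% |
| 87 v 5 (planned 5% of 92) | 90% | 81% | 59% |

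A looser screen misses less. At 64 v 39 and 0.5 SD the miss rate is 21% at α = 0.10 and 12% at α = 0.20.

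**Factor acting in the intervention arm only.** This assumes a 52/51 split of the 103 dyads, and that the 27 intervention dyads used as the denominator for the interviews in Results are that arm's completers. The arm's loss is then 52 − 27 = 25. Within the arm (27 v 25) a 0.5 SD difference is missed 58% of the time.

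**Consequence of a miss.** Shift in the completer mean = dropout share × completer-dropout difference × correlation with the outcome. The difference to insert is not the full 0.5 SD, because a non-significant result limits what was realised in the sample: at 64 v 39, anything above about 0.40 SD is significant. By simulation at a true 0.5 SD, the mean realised difference given a miss is about 0.27 SD (64 v 39) and 0.32 SD (27 v 25).

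- 64 v 39: 39/103 × 0.27 × 0.4 = 0.04 SD.
- 27 v 25: 25/52 × 0.32 × 0.4 = 0.06 SD.
- Planned 5% loss, even with the full 0.5 SD: 0.05 × 0.5 × 0.4 = 0.01 SD.

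All of these are before any correction from earlier scores in the mixed model. For scale, the standard error of a 27 v 37 comparison is √(1/27 + 1/37) = 0.25 SD.

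**The case against.** A reader might infer that the plan treats a negative screen as proof that dropout is harmless. It does not: it states the opposite worry, and a negative screen only leaves the default analysis in place. That default is not naive. The baseline and midtest scores are responses in the likelihood-based model, so dropout that depends on them is accommodated whatever the screen finds. Of the 39 dyads without a posttest, 90 − 64 = 26 had completed the midtest. This objection stands and narrows the gap considerably. It does not close it, since the planning correlation over time is only 0.30 and earlier scores therefore stand in only partly for an omitted factor.

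A reader might also take 81% as the screen's miss rate. That figure belongs to a 5% loss, where the shift is about 0.01 SD and which did not occur.

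The test and its level are borrowed from the arm comparisons in Statistical Analysis. The attrition passage does not state them, and its wording does not exclude factors specific to one arm. This is right, and the percentages are conditional on it. The exact test, threshold and factor list may also properly sit in an analysis plan that is not shown. Their absence is not the point made here; the conditional rule is stated in the article itself.

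**Conclusion.** The point holds as a minor one. The plan lets a screen of limited power decide whether a baseline predictor of dropout is adjusted for and whether multiple imputation is used. At the reported loss the screen would miss a 0.5 SD difference about 32% of the time at posttest and 61% at midtest; over 0.3 to 0.8 SD the ranges are 69% to 3% and 83% to 24%. The likely shift after a miss is about 0.04 to 0.06 SD before model correction, small against a standard error of about 0.25 SD. The upper figure refers to a factor acting in one arm. A factor acting alike in both arms would largely cancel.

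These sizes rest on the assumed 5% t test, the 0.5 SD difference, the 0.4 correlation and, for the arm figure, the 52/51 split with 27 intervention completers. The document does not support saying that dropout goes unhandled or that the result is seriously biased. It supports saying that a test-triggered adjustment is a poorer rule than a fixed one that costs almost nothing.

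**What to change.** Remove the condition that a factor must first be detected. Fix a short list of baseline variables already collected, for example age, education and self-reported health (Measurement, Overview), plus AD8 for older adults (Sampling and Recruitment Plan). Include them in every mixed model, or in the imputation model by arm, whatever the attrition test shows. Since analysis was already under way when the article was written, record when the list was fixed.

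Keep the baseline outcome score as a response. It should not also be added as a covariate, since it would then stand on both sides of the model.

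Keep the attrition analysis as description: report completer-dropout differences by arm as estimates with 95% CIs, and do not conclude from a non-significant test that dropout was random.

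The cost is a sentence or two in the analysis plan and a few degrees of freedom. No new data are needed.
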